##### Demographic, clinical, neurophysiological, neuropsychological and biological data analysis

Socio-demographic data will be compared between the active rTMS and the sham rTMS groups, and also between the ‘responder’ and ‘non-responder’ groups, using a two-sample *t* test (Student’s *t* test) or a χ^2^ test.

To control for the rTMS treatment efficacy, a repeated-measures analysis of variance (ANOVA) will be performed on AHRS with time (before/after rTMS) as the within-subject factor and group (active rTMS/sham rTMS) as the between-group factor (based on the per-protocol principles). The same strategy will be followed for clinical, neurophysiological, neuropsychological, and biological data. Post-hoc pair-wise comparisons will be performed using a two-sample *t* test (Student’s *t* test) or χ^2^ test. Bonferroni correction will be applied as a multiple comparison adjustment to reduce the chances of a false positive result. Normality of data distribution (Shapiro–Wilk’s test) and equality of variances (Levene’s test) will be previously verified. All data will be presented as mean ± standard deviation. For all tests, statistical significance will be set as *p* ≤ 0.05.

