##### Clinical assessments

The Auditory Hallucinations Rating Scale (AHRS) is widely used to assess the presence and severity of AVH across seven items investigating frequency, level of reality, loudness, number of voices, length of the content, level of distraction, and distress [27]. The HCS is linked to the AHRS and evaluates the percentage of AVH change [33]. On a scale from 0 to 20, a default score of 10 will be attributed to a narrative description of the patient AVH prior to the rTMS sessions (baseline, W0). For the re-assessment of the AVH following rTMS treatment, scores will be evaluated again, and ascribed lower values (with 0 corresponding to total absence of AVH) if AVH severity decreases, whereas a higher score will be ascribed if AVH severity is worse (with 20 indicating twice the severity of AVH compared to baseline). The scoring system of the HCS allows estimation of a percentage of AVH change after rTMS treatment. A score of 5 or less ascribed by the medical evaluator at W3 indicates a decrease of 50% or more of AVH. In this case, the patient will be considered a ‘responder’. Otherwise, the patient will be considered a ‘non-responder’. The AHRS and HCS will be employed to assess the severity of AVH and the efficacy of rTMS therapy. AHRS and HCS will be recorded at each time point of this study (W0, W3, W7, and W15).

The Positive And Negative Syndrome Scale [34] is a 30-item scale, which is widely used to assess the overall disease severity of schizophrenia such as psychosis-related symptoms (hallucinatory behavior, delusions, emotional withdrawal, stereotyped thinking) and general psychopathology (including ‘poor attention’, depression and anxiety). In addition, the Psychotic Symptom Rating Scale (PSYRATS [35]), a 17-item scale, will be employed to evaluate the psychotic symptoms (hallucinations and delusions) and the Scale for the Assessment of Negative Symptoms [36], a 25-item scale, will be used to assess the negative symptoms in schizophrenia.

Comorbid depressive symptoms will be investigated with the Beck Depression Inventory [37], a 13-item, self-report rating inventory and the Calgary Depression Scale for Schizophrenia, a 9-item structured interview scale [38].

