## Discussion

Several meta-analyses support significant reduction of AVH severity in schizophrenia following a multi-day 1 Hz rTMS regime [12–19], spurring hopes for rTMS for this indication. Nonetheless, the high level of interindividual variability in clinical responses has weakened enthusiasm about its clinical efficacy and the topic remains debated. In this context, the identification of biomarkers predictive of positive clinical response could help clarify the situation and provide more effective, suitable, and customized treatments for AVH in schizophrenia. Moreover, by identifying patients who are most likely to respond before therapy is applied, clinical indications could be fine-tuned and, thus, general outcomes could be improved. In our trial, functional and structural neuroimaging datasets recorded prior and following the rTMS therapy will be employed to better characterize mechanisms underlying the emergence of AVH, evaluate the impact of a multiday rTMS regime, and gauge ability to drive enduring recovery.

The protocol proposed for our trial follows previously established recommendations on therapeutic uses of rTMS for the treatment of AVH, using 1 Hz rTMS over the left TPJ region [66]. However, to date, no clear guidelines exist to titrate other stimulation parameters, such as rTMS intensity (established between 90% and 100% of the MT) or the number of total sessions (or cumulated sessions per day) necessary to achieve stable recovery in the shortest possible period (10 sessions over 1–2 weeks remain the most common protocol), which vary greatly across studies [66]. Moreover, no established guidelines seem to exist yet with regards to the maximal number of pulses to be delivered per session. Nonetheless, to our knowledge, no study included in the guidelines for therapeutic use of rTMS [66] or cited in the 11 meta-analyses addressing the effect of rTMS on auditory hallucinations in schizophrenia from 2007 to 2018 [13–18, 67–69] seem to use more than 1200 pulses per session. To remain consistent with prior literature and convince the Institutional Review Board of the safety of our interventions we took the decision to align ourselves with established recommendations or prior peer-reviewed publications in the field.

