It is also important to mention that, although the main and primary outcome goal of our project is the identification of structural and functional brain biomarkers of clinical response, our rTMS protocol includes a sham rTMS group to control for the placebo effect of rTMS therapy on AVH. In an attempt to meet the main objective of our trial within a reasonable time period, which is to identify biomarkers associated with clinical response, we here decided to assign as many participants as we could possibly recruit and treat (given sample size calculations and allotted time and resources) to an active rTMS treatment. Consequently, an unequal lower number of patients (*n* = 10 patients, i.e., 22% of the final sample) will be randomized to the sham rTMS group which is used to verify the known lack of recovery of enduring AVH when no effective intervention is applied.

In our study, we propose a stratified randomization based on sex only although a stratification by sex and age would be more complete. Nonetheless, we are bound to study two groups (active rTMS *n* = 35 and placebo rTMS *n* = 10) with an unequal number of patients, and therefore the stratification on sex as well as age ranges would be more complex. We have currently defined two strata – male and female. If we were to add the variable ‘age’, we would have to deal with a much higher number of strata (two for gender and, for example, three for age: 18–35, 35–50, and 50–65 years old), and this would significantly slow down or seriously compromise the recruitment process in the time allotted to complete the study. Nonetheless, sex and age will be added as covariables in the statistical analyses.

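### The two-level before/after ANOVA on AHRS does not condition on baseline, the promised sex and age covariates are absent from it and cannot enter the stated t tests, and no analysis names W7 or W15

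*Protocol article*

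**What the plan says.** The section on demographic, clinical, neurophysiological, neuropsychological and biological data analysis fixes the efficacy check: "a repeated-measures analysis of variance (ANOVA) will be performed on AHRS with time (before/after rTMS) as the within-subject factor". The other factor is the randomized arm, and the analysis is restricted to patients who followed the protocol. It then extends the approach: "The same strategy will be followed for clinical, neurophysiological, neuropsychological, and biological data". For follow-up tests it states: "Post-hoc pair-wise comparisons will be performed using a two-sample". The sentence goes on to name Student's version of that test, or a chi-square, and a Bonferroni correction applies. The section names no covariate, no paired test and no visit beyond before and after.

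The Discussion explains why randomization is stratified on sex alone and adds: "Nonetheless, sex and age will be added as covariables in the statistical analyses".

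The section on resting-state functional connectivity analysis specifies two-sample t tests twice: on the z-score maps and on the intrinsic connectivity parameters from dynamic causal modelling. The Data analysis section makes these comparisons of responders with non-responders.

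On timing, the Clinical assessments section says "AHRS and HCS will be recorded at each time point of this study (W0, W3, W7, and W15", and adds that the scales serve to follow symptoms through the study.

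**The concern.** Four features of the stated methods deserve attention.

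- **Baseline.** A two-level repeated-measures ANOVA uses baseline AHRS as one level of the time factor but does not condition on it. With only 10 sham patients, precision is scarce and chance imbalance at baseline is likely to be appreciable.
- **Covariates.** Sex and age are promised for the analyses generally. They appear in no stated model, and some of the named tests have no place for them. This matters most for responders versus non-responders, a comparison that is not randomized and can be confounded by sex and age. Functional connectivity is listed under the primary outcome measures, so it is not a side issue.
- **Post-hoc tests.** The model has a within-patient factor, but only independent-group tests are named.
- **Follow-up.** AHRS is collected at four time points, and the stated time factor names only before and after.

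At stake are the power and clarity of the active-versus-sham check, the adjustment of the connectivity comparisons, and whether the follow-up data receive a planned analysis.

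**Working it through.** **Inputs from the article.** 35 active and 10 sham patients (35/45 = 78%, 10/45 = 22%, as stated). The article gives no power or sample size for the AHRS comparison, so there is no figure of its own to reproduce here. Its calculation of 32, raised to 35, concerns fractional anisotropy.

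**Assumptions.** The before/after correlation rho (0.3 to 0.8), the active-versus-sham effect d (0.8, in SDs of a single AHRS measurement), and equal SD, set to 1, before and after. The article gives none of these.

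**1. What the ANOVA tests.** On one simulated 35/10 data set, the time-by-group F was 3.4698 and the squared t statistic on change scores was 3.4698 (p = 0.0693 both ways). Adding sex and age, each crossed with time, gave t = -1.746 for the arm effect. Regressing change on arm, sex and age gave the same value. So the ANOVA is a change analysis, and it could carry the covariates.

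**2. Cost of not conditioning on baseline.** Residual variance is 2(1-rho) for change and 1-rho^2 with baseline adjustment. The ratio is (1-rho^2)/(2(1-rho)) = (1+rho)/2. Power uses the noncentral t at 35 versus 10, two-sided 5%.

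| rho | Change | Adjusted | Ratio | Power, change | Power, adjusted |
|---|---|---|---|---|---|
| 0.3 | 1.40 | 0.91 | 0.65 | 45% | 63% |
| 0.5 | 1.00 | 0.75 | 0.75 | 59% | 71% |
| 0.7 | 0.60 | 0.51 | 0.85 | 80% | 86% |
| 0.8 | 0.40 | 0.36 | 0.90 | 93% | 95% |

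Estimating the baseline slope with N = 45 multiplies the adjusted variance by about 1 + 1/(45-4) = 1.024. The ratios become 0.65 x 1.024 = 0.67 to 0.90 x 1.024 = 0.92. A 20,000-run simulation gave 0.66 to 0.92, with adjusted power of 62%, 70%, 86% and 95%. The gain is real but shrinks as rho rises.

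**3. Chance imbalance.** The standard error of the baseline mean difference is sqrt(1/35 + 1/10) = 0.36 SD. Given a baseline difference delta, the change analysis is shifted by (1-rho) x delta in absolute size. With a one-standard-error imbalance and rho = 0.5, that is 0.5 x 0.36 = 0.18 SD. Baseline adjustment removes this shift.

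**4. Unpaired test on paired data, if used.** With n patients measured twice, the unpaired standard error is sqrt(2/n) and the correct one is sqrt(2(1-rho)/n). The ratio is 1/sqrt(1-rho). Simulation: 20,000 runs, n = 35, shift of 0.5 SD for power.

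| rho | SE ratio | Type I error, unpaired | Power, unpaired | Power, paired |
|---|---|---|---|---|
| 0.3 | 1.20 | 2.0% | 55% | 68% |
| 0.5 | 1.41 | 0.7% | 56% | 82% |
| 0.7 | 1.83 | 0.1% | 57% | 96% |

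**5. Covariates, side by side.** The Discussion promises sex and age. The ANOVA on AHRS lists time and group only. The functional connectivity tests are two-sample t tests, which have no covariate term. The linear mixed-effects model for fractional anisotropy, in the structural connectivity section, can take covariates.

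**6. Visits.** AHRS is recorded at W0, W3, W7 and W15. If after means W3, the two-level factor uses two of the four. No analysis in the article names W7 or W15.

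**The case against.** A change analysis is valid and unbiased over randomization, so point 2 concerns efficiency. That is correct. A reader might infer that baseline is ignored; it is not, because the before level is the baseline AHRS.

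A reader might also infer that none of the planned models can carry sex and age. That goes too far: the ANOVA extends readily, and the structural connectivity section already uses a linear mixed-effects model. A condensed article need not repeat the covariates in each paragraph. What stands is that the tests stated for functional connectivity are of a type that cannot honour the promise.

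It is tempting to say that within-arm before/after comparisons are specified with an unpaired test. The article does not say which pairs are compared. Two-sample tests are right for active versus sham at one visit, so the criticism is conditional. The error would also be conservative.

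Finally, a reader might cite the Discussion's wish to "evaluate the impact of a multiday rTMS regime, and gauge ability to drive enduring recovery" as a stated durability aim for AHRS. That sentence concerns neuroimaging, which is recorded only at W0 and W3. The Aims section states no durability objective. The section on blood samples counts W3, W7 and W15 all as after the regime, so before/after is not clearly W3 only, and a fuller plan may hold a follow-up model. The firm statement is that no analysis given here names W7 or W15, although AHRS is collected then to follow symptoms.

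**Conclusion.** The point holds and should be acted on, though it does not threaten the trial's main result. The stated ANOVA uses baseline only through change. Conditioning on it would reduce residual variance by 10% to 35% (8% to 33% after the small cost of estimating the slope) for rho from 0.8 to 0.3. At an assumed d of 0.8, that adds between 2 and 18 percentage points of power. Both rho and d are assumptions.

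The covariate promise and the two-sample t tests for functional connectivity do not agree. This needs no assumption. The pairing problem depends on which post-hoc comparisons are intended and would cost power only. The follow-up visits lack a stated analysis in this article.

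The scope is a secondary efficacy check plus the functional connectivity comparisons. The fractional anisotropy analysis can already carry covariates, and no sample-size figure changes.

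**What to change.** 1. Analyse AHRS and the other repeated secondary scales with a baseline-adjusted model: either ANCOVA at W3, or a mixed model over the post-treatment visits with baseline value, arm, visit, arm-by-visit, sex and age. For each measure, use the visits at which it is actually recorded; the Discussion, for example, says detailed neurophysiology is not done at W7 and W15. Report the arm difference at W3 first, then W7 and W15.
2. Name the post-hoc comparisons. Take change within an arm from model contrasts or paired tests, and keep independent-group tests for active versus sham at a given visit.
3. Replace the two-sample t tests on responder versus non-responder functional connectivity (z maps and dynamic causal modelling parameters) with linear models containing sex and age.
4. Leave the descriptive socio-demographic comparisons as they are. They include age and sex, so adjusting them for age and sex would make no sense.

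The cost is analysis wording and code. No new data, visits or patients are needed.

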## Discussion

Several meta-analyses support significant reduction of AVH severity in schizophrenia following a multi-day 1 Hz rTMS regime [12–19], spurring hopes for rTMS for this indication. Nonetheless, the high level of interindividual variability in clinical responses has weakened enthusiasm about its clinical efficacy and the topic remains debated. In this context, the identification of biomarkers predictive of positive clinical response could help clarify the situation and provide more effective, suitable, and customized treatments for AVH in schizophrenia. Moreover, by identifying patients who are most likely to respond before therapy is applied, clinical indications could be fine-tuned and, thus, general outcomes could be improved. In our trial, functional and structural neuroimaging datasets recorded prior and following the rTMS therapy will be employed to better characterize mechanisms underlying the emergence of AVH, evaluate the impact of a multiday rTMS regime, and gauge ability to drive enduring recovery.

The protocol proposed for our trial follows previously established recommendations on therapeutic uses of rTMS for the treatment of AVH, using 1 Hz rTMS over the left TPJ region [66]. However, to date, no clear guidelines exist to titrate other stimulation parameters, such as rTMS intensity (established between 90% and 100% of the MT) or the number of total sessions (or cumulated sessions per day) necessary to achieve stable recovery in the shortest possible period (10 sessions over 1–2 weeks remain the most common protocol), which vary greatly across studies [66]. Moreover, no established guidelines seem to exist yet with regards to the maximal number of pulses to be delivered per session. Nonetheless, to our knowledge, no study included in the guidelines for therapeutic use of rTMS [66] or cited in the 11 meta-analyses addressing the effect of rTMS on auditory hallucinations in schizophrenia from 2007 to 2018 [13–18, 67–69] seem to use more than 1200 pulses per session. To remain consistent with prior literature and convince the Institutional Review Board of the safety of our interventions we took the decision to align ourselves with established recommendations or prior peer-reviewed publications in the field.

In this protocol, we chose to administer two sessions of 1200 pulses of 1 Hz rTMS per day (interleaved by a TMS-free 1 h interval) across two consecutive weeks, from Monday to Friday (10 days in total). The doubling of daily rTMS sessions aims to increase the total number of delivered stimuli, enhance effect magnitude and duration, and shorten stimulation regime duration. To this regard, fundamental studies evaluating changes of primary motor cortex excitability in healthy participants have shown, for example, that the higher the number of stimuli, the longer the duration of rTMS inhibitory effects [70, 71].

During the description of the study to patients, the investigators will clearly specify that rTMS therapy occurs daily over two consecutive weeks (except on weekends). After the inclusion phase, a prospective schedule for the rTMS sessions (and other appointments) will be proposed to be approved by each patient. If necessary, the appointment time can be modified and adapted to the patient requirements. If once duly informed about the schedule, a patient declares that they cannot attend all the planned rTMS sessions over 2 weeks, they will not be included in the study. In that case, an active rTMS treatment with a more flexible schedule can be offered to these patients, outside this research protocol. If the participant misses an appointment, it is possible to shift the sessions of a day. In case a patient stops attending the rTMS sessions before the end of the treatment or if they are unable to attend to more than two consecutive rTMS sessions for any reason, investigators will consider that the established research protocol is no longer respected. The participant will then be withdrawn from the study and their data will not be considered in the analyses. This situation will not suppose any change for the medical attention or treatment the patient undergoes in our institution.

Regarding potential rTMS targets in AVH, work published by Hoffman et al. [25, 72] has shown that active (but not sham) rTMS over the left TPJ induces higher levels of clinical improvement than stimulation on temporal and frontal areas. Therefore, the current protocol will employ MRI-based neuronavigation to localize the Wernicke’s area in the left TPJ according to specific spatial coordinates (MNI coordinates: x = − 69, y = − 41, z = 11) on each individual participant MRI.

It is also important to mention that, although the main and primary outcome goal of our project is the identification of structural and functional brain biomarkers of clinical response, our rTMS protocol includes a sham rTMS group to control for the placebo effect of rTMS therapy on AVH. In an attempt to meet the main objective of our trial within a reasonable time period, which is to identify biomarkers associated with clinical response, we here decided to assign as many participants as we could possibly recruit and treat (given sample size calculations and allotted time and resources) to an active rTMS treatment. Consequently, an unequal lower number of patients (*n* = 10 patients, i.e., 22% of the final sample) will be randomized to the sham rTMS group which is used to verify the known lack of recovery of enduring AVH when no effective intervention is applied.

In our study, we propose a stratified randomization based on sex only although a stratification by sex and age would be more complete. Nonetheless, we are bound to study two groups (active rTMS *n* = 35 and placebo rTMS *n* = 10) with an unequal number of patients, and therefore the stratification on sex as well as age ranges would be more complex. We have currently defined two strata – male and female. If we were to add the variable ‘age’, we would have to deal with a much higher number of strata (two for gender and, for example, three for age: 18–35, 35–50, and 50–65 years old), and this would significantly slow down or seriously compromise the recruitment process in the time allotted to complete the study. Nonetheless, sex and age will be added as covariables in the statistical analyses.

Importantly, in our trial, we will define clinical response to active rTMS as a reduction of 50% in the HCS measured at the end of rTMS treatment (W3) compared to baseline evaluation (W0); this criteria of response is commonly found in rTMS studies in schizophrenia [27, 52, 73, 74]. Nevertheless, the response criteria may vary in some studies in which ‘responders’ are defined as patients showing a reduction of 30% in the PSYRATS [75, 76] or the AHRS scale [77]. Even though different scales such as the PSYRATS or the AHRS scales have both been shown to exhibit good psychometric reliability, the HCS seems to be the most sensitive to rTMS effects on AVH [13, 69] and thus will be applied to classify patients as ‘responders’ or ‘non-responders’ to rTMS. Using this same criterion to classify patients with positive (for ‘responders’) or negative (for ‘non-responders’) clinical responses to rTMS, our protocol predicts 40–50% success rate, thus proving beneficial for at least half of actively stimulated patients.

With regards to the neuroimaging datasets, three sequences (structural 3D-T1 MRI, functional rs-fMRI, and DWI) will be acquired prior and following the multiday rTMS protocol. MRI acquisition sessions will take approximately 30 min for each patient. Schizophrenia patients could have difficulty staying quiet and motionless for a long time in an unnatural environment such as the MRI bore. Thus, the final rs-fMRI sequence chosen, which is relatively short compared to similar studies in healthy participants, is the result of a tight compromise that aims to optimize the investigation of brain functional connectivity in this specific population.

In our trial, we will also determine the levels of BDNF in blood serum for each subject at baseline (W0) and at several stages following the end of the rTMS regime (W3, W7 and W15). BDNF plays a key role in neuronal survival, neurogenesis, the growth of dendrites and axons, synapse formation and synaptic strength gain [78]. Thus, increases of this factor may likely reflect or impact the level of brain plasticity and excitability changes induced by rTMS [49], which could potentially correlate with the magnitude of rTMS effect on AVH in schizophrenia patients. Moreover, baseline blood levels of BDNF could be predictive of clinical response.

Our trial also integrates an evaluation of several cognitive domains, which can either be altered in schizophrenia patients or could be modified by the 10-day rTMS treatment delivered to the left TPJ, thus informing about the cognitive domain selectivity of stimulation. The completion of all these tests takes at least 2 h at baseline (W0) and post rTMS regime (W3) evaluations. For practical reasons and to ensure patient compliance and reliability, evaluations have been planned and adapted to last no more than 1 h. Consequently, several tests (particularly the Hanoi Tower, the verbal memory task, the task of Corsi or MEM battery, and an autobiographical memory task) have been removed. For the same reason, detailed neurophysiological measurements will not be performed at W7 and W15 post rTMS treatment.

Another point we discussed about neuropsychological assessment is the estimation of a patient’s premorbid intellectual functioning. A very detailed assessment of premorbid intellectual status was not included in our study since it would increase the time spent on cognitive assessments for patients. Indeed, this assessment takes approximately 90 min using the Wechsler Adult Intelligence Scale or 40 min using a short form of this. An alternative, the National Adult Reading Test, is used for estimating premorbid intelligence levels and could take just a few minutes. Nonetheless, this test consists of 50 words, graded in difficulty, whose pronunciation cannot be determined from their spelling. Unfortunately, our protocol will include patients with sufficient knowledge of the French language although not necessarily be French-native speakers and, as such, the outcomes of the National Adult Reading Test could be biased.

In conclusion, the current clinical trial will investigate how brain structural and functional connectivity at the network level may influence rTMS impact on AVH severity, and also address how the rTMS treatment can modulate brain function and induce clinical improvement for this symptom in schizophrenia patients. Our study will provide new insights to treat AVH with rTMS in schizophrenia and, by identifying structural and functional connectivity biomarkers of the clinical response to rTMS stimulation in AVH, eventually contribute significantly to refine this indication and allow the customization of therapeutic protocols.

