#### Exit criteria

Patients will be withdrawn from the trial if (1) they simply wish to stop participation; (2) they could not undergo the first MRI session; (3) they did not complete the rTMS sessions; and (4) if they suffered from worsening symptoms.

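### Patients who stop rTMS early are left out of every analysis and the active-versus-sham test is per-protocol, so both key comparisons depend on events after randomisation that may be linked to outcome

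*Protocol article*

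**What the plan says.** Four parts of the protocol article bear on this.

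- **Discussion (missed sessions).** The rule applies to a patient who "stops attending the rTMS sessions before the end of the treatment or if they are unable to attend to more than two consecutive rTMS sessions", whatever the reason. The consequence is explicit: "The participant will then be withdrawn from the study and their data will not be considered in the analyses". A missed day may be shifted.
- **Exit criteria.** Among the grounds for withdrawal are that "they did not complete the rTMS sessions; and (4) if they suffered from worsening symptoms". This section says nothing about what happens to the data.
- **Demographic, clinical, neurophysiological, neuropsychological and biological data analysis.** The repeated-measures ANOVA of AHRS, active against sham, is "based on the per-protocol principles". The same strategy is extended to the other non-imaging data.
- **Clinical assessments.** An HCS of 5 or less at W3 makes a responder. "Otherwise, the patient will be considered a ‘non-responder". Baseline is fixed at 10, and "a higher score will be ascribed if AVH severity is worse", on a scale running to 20 ("with 20 indicating twice the severity of AVH compared to baseline").

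The primary outcome is baseline FA, responders against non-responders, and the Sample size and Data analysis sections confine it to the active arm. The baseline scan is taken before treatment starts (Study design). The article describes no analysis that retains withdrawn patients.

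**The concern.** Whether a patient completes the course is known only after randomisation, and it can depend on how the patient is doing. Someone who stops because the voices are no better, or are worse, would be a non-responder under the HCS rule. Leaving such patients out selects on the variable that defines the two primary groups.

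The exclusion is also not forced by missing imaging. The primary measurement is a scan that these patients have already had, and failure to undergo it is a separate exit criterion.

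Three things are at stake: the reported response rate, the size and precision of the responder/non-responder contrast in FA, and the standing of the active-versus-sham test. That test loses the protection of randomisation once patients are removed for what happened during treatment. With 10 sham patients, each exclusion there removes 10% of the arm.

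**Working it through.** **1. The plan's own figures (Sample size section).** Active-arm need 32, drop-out 10%, recruitment 35. Check: 32/0.9 = 35.6 and 32 × 1.1 = 35.2, so 35 is reproduced to within one patient. Split: 35 × 0.40 = 14 responders and 35 × 0.60 = 21 non-responders, as stated. The 32 cannot be reproduced because no FA difference or SD is given.

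**2. Counts after the planned loss.** 35 × 0.9 = 31.5 patients remain, so 3.5 are lost.
- Loss unrelated to response: 31.5 × 0.40 = 12.6 responders and 31.5 × 0.60 = 18.9 non-responders. The response rate stays at 40%, but responders fall below the section's stated minimum of 14 per group.
- Loss entirely among non-responders: 14 against 17.5. The response rate becomes 14/31.5 = 44%, and 3.5/21 = 17% of non-responders disappear.
- If 2, 3, 4 or 5 non-responders are excluded: 14/33 = 42%, 14/32 = 44%, 14/31 = 45%, 14/30 = 47%.

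**3. Effect on the FA contrast (illustration).** Assume that response is normally distributed, that the top 40% are responders, and that baseline FA is linearly related to response with correlation r. None of this is in the protocol.
- Mean response in SD units: responders +0.966, all non-responders −0.644, gap 1.610.
- With the worst 10% of all active patients removed, the non-responder mean is −0.422 and the gap 1.388. The ratio 1.388/1.610 = 0.86, so the contrast shrinks by about 14%.

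The raw FA difference is r times the gap. Dividing by the within-group SD (by simulation, 2 million draws) gives d. Power is for a two-sided t test at 0.05.

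| Scenario | r = 0.4 | r = 0.5 |
|---|---|---|
| No loss, 14 v 21 | d 0.68, power 48% | d 0.88, power 69% |
| Random 10% loss (12.6 v 18.9, or 14 v 17 with no selection) | d 0.68, power 44% | d 0.88, power 64–65% |
| Only the single worst patient lost, 14 v 20 | power 44% | power 65% |
| Worst 10% lost, 14 v 17 | d 0.59, power 36% | d 0.77, power 54% |

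At r = 0.5 the worst case costs 69 − 54 = 15 points, of which about 5 (69 − 64) are ordinary loss of numbers. At r = 0.4 the figures are 48 − 36 = 12 and 48 − 44 = 4. Selection accounts for the rest.

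**4. Effect on the active-arm mean (illustration on the HCS, whose anchors the document gives).** Assume responders score 4 and other non-responders 9.
- One worsened patient at 12: all patients (14×4 + 20×9 + 12)/35 = 7.09; after exclusion 236/34 = 6.94, a fall of 0.14 (from unrounded means).
- Four worsened patients at 20: (56 + 17×9 + 80)/35 = 8.26; after exclusion 209/31 = 6.74, a fall of 1.5.

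This makes active rTMS look better unless sham loses patients in the same way.

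**5. The two completion rules side by side.** The Exit criteria remove anyone who did not complete the sessions. The Discussion lets a day be shifted and removes those who stop or miss more than two sessions in a row which, at two sessions a day, is more than one treatment day. A patient who misses one or two sessions, never makes them up and finishes otherwise is out under the first rule and apparently in under the second.

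**The case against.** A reader might infer that every patient who worsens has their data deleted and that the biomarker contrast is therefore known to be biased. The documents do not support that.

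- The text says that data are not considered in the analyses. It does not speak of deletion, and it says this only of patients who stop or miss sessions.
- For worsening, the Exit criteria say only that the patient is withdrawn. Exclusion is an inference: someone withdrawn mid-course has not completed and is not per-protocol. A patient first rated worse at W3 after 20 sessions is not clearly covered, and the HCS range up to 20 suggests that such patients are expected to be rated.
- Worsening is not defined there as worsening of AVH, so it need not mean an HCS above 10.
- The 36–54% power is a ceiling on the harm. It places all drop-out on the worst outcomes, whereas the exit criteria also include patient wish and failure to undergo the first MRI. Losing one extreme patient costs about as much as the planned random loss.
- Attenuation requires FA to track response into the worst tail. The protocol hypothesises only that the two groups differ.
- For an exploratory question about response to a full course, a full-course set is defensible. Calling someone who left after one session for unrelated reasons a non-responder would itself misclassify.
- The two completion rules can mostly be read together, with the Discussion specifying the Exit criteria. Only missed sessions that are never made up stay ambiguous.

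These points stand, and they limit the size and wording of the concern. They do not remove it: the exclusion of early stoppers and the per-protocol basis are stated outright, and no analysis retaining these patients is stated beside them.

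**Conclusion.** The concern holds in limited form; it is a should-fix. As written, both the responder comparison and the active-versus-sham test are conditioned on completing treatment. Exclusions related to outcome would remove non-responders selectively, and the AHRS test is not a comparison of the groups as randomised.

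The size cannot be derived from the document. The shift in response rate from 40% to 44% assumes that the whole planned loss is non-responders. The power figures also assume a correlation of 0.4 to 0.5 between FA and response; without such a correlation there is no contrast to attenuate and only numbers are lost. The direction of any bias in the active-versus-sham test depends on who leaves the sham arm. Because that test is a supporting check and the bias in the primary contrast is plausible but not demonstrated, a higher severity is not warranted.

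**What to change.** Separate stopping treatment from leaving the analysis.

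1. **Active versus sham.** Analyse AHRS in all randomised patients in their assigned arm. Seek the W3 HCS and AHRS ratings from those who stop. Keep the per-protocol set as a sensitivity analysis.
2. **Responder comparison, active arm only.** Retain patients with a usable baseline MRI. Classify them by W3 HCS where it was obtained, and count those withdrawn for worsening or lack of benefit as non-responders. Report the full-course set, and the handling of patients who stop for unrelated reasons, as sensitivity analyses. Sham patients stay out of this contrast, as the Sample size and Data analysis sections intend.
3. **Completion.** Reconcile the Exit criteria with the Discussion so that one definition governs the per-protocol set, and state how worsening first seen at W3 is handled.

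The cost is analysis-set wording, a recorded reason for stopping, and a few extra ratings. The downside is some dilution of the full-course contrast, which the sensitivity analysis would show. No rule on when treatment stops is changed.
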